### Outcomes

#### Primary outcome

The primary outcome of this study is adherence to the mobile app-based physical activity intervention, measured using three indicators: the number of logins per week, the percentage of weekly goals set and the percentage of questionnaires completed by the participant during the 6 months. Adherence will be considered good if the number of logins per week does not decrease by more than 33% between the first and the last month and if at least 50% of the weekly goals are set and questionnaires are completed over the intervention.

### Secondary outcomes

Retention will be calculated as the number of dropouts over time during the 6 months. A retention of ≥ 33% of participants at the end of the 6 months will be considered a successful outcome. Moreover, the acceptability of the mobile app and the intervention by the study participants will be assessed qualitatively through a combination of open- and closed-ended questions. This will cover usefulness, most motivating features, user-friendliness, adaptability to condition, intent to continue physical activity and suggestions for improvement. Acceptability will be considered good if ≥ 70% of responses regarding usefulness, user-friendliness and adaptability to condition are positive. Feasibility will be validated if adherence, retention and acceptability meet the positive outcomes specified above.

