**Methods:**

The PIANISSIMO study is a longitudinal, interventional feasibility study conducted through a dedicated mobile app. A total of 151 participants with hip or knee osteoarthritis will be included. The app will collect data and deliver the intervention. Data will be collected through questionnaires (i.e. demographic data, osteoarthritis history, sport history, pain and functional capacities, app evaluation) and from Apple Health/Google Fit apps. The PIANISSIMO study will use a 6-month physical activity intervention based on the *Capability**, **Opportunity**, **Motivation–Behaviour* change theory. Participants will receive a text notification on a daily basis; they will be asked to set their daily steps goal for the next week, and the mobile app will deliver feedback on daily step count and whether the goal of the week has been reached. The primary outcome of this study is the adherence (i.e. connection log and rate of answered questionnaires) to the app-based physical activity intervention. Retention will be calculated as the number of drop-outs over 6 months of follow-up. Moreover, the acceptability of the app and intervention by the study participants will be evaluated through a questionnaire.

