### Sample size

Assuming a minimum adherence rate of 67% in the last month, a 95% confidence level and an acceptable margin of error of 7.5%, a minimum of 151 participants with hip or knee OA is required.

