At the end of the intervention, participants will be invited to give their feedback about the mobile app through a qualitative standardised questionnaire. Participants will be asked if the mobile app helped them increase their physical activity level, if they think they could maintain the actual level of physical activity without the intervention, what motivated them the most (goal setting, text notifications, both, nothing), if they liked the app and why, if they found that the app was adapted to their health condition, if they would recommend the app and how they heard about it. A free comment section will also be available. After 2 weeks without any interaction (i.e. no response to the questionnaire or connexion to the mobile app), the participant will be considered a drop out.

During the subsequent 6-month follow-up period, the pain evaluation questionnaire will be sent randomly twice a month (Fig. 1).

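### The retention success mark of ≥33% does not fit the 67% last-month adherence premise on which the sample size rests

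*Protocol article*

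**What the plan says.** The Sample size section of the protocol article sets the planning premise: "Assuming a minimum adherence rate of 67% in the last month", with "a 95% confidence level and an acceptable margin of error of 7.5"%. It concludes that "a minimum of 151 participants with hip or knee OA is required". The abstract treats the same number as the number entered: "A total of 151 participants with hip or knee osteoarthritis will be included". Neither place adds an allowance for drop-out.

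Under Primary outcome, adherence has three indicators: logins per week, weekly goals set and questionnaires completed. The login indicator is met if the weekly number "does not decrease by more than 33% between the first and the last month". The other two need at least 50% each. The section does not say whether these are computed among everyone enrolled or only among those still in the study.

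Under Secondary outcomes, the measure is "Retention will be calculated as the number of dropouts over time during the 6 months", and Table 2 likewise lists the number of drop-outs as the measurement. The next sentence sets the mark: "A retention of ≥ 33% of participants at the end of the 6 months will be considered a successful outcome". Feasibility is confirmed only if adherence, retention and acceptability all reach their marks.

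Under Follow-up data, after 2 weeks with no questionnaire response and no connection to the app, "the participant will be considered a drop out".

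**The concern.** A study sized on at least 67% adherence in its last month would be expected to treat a loss of two thirds of its participants as a failure of retention. This one counts it as a success. Someone who has dropped out is, by the protocol's definition, no longer using the app, so retention limits how many can be adherent at the end. The retention mark sits at about half the level that the sizing premise needs.

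The wording adds doubt about what was meant. Retention is described through its opposite, and under Primary outcome the figure of 33% is a tolerated fall, which leaves 67%. The two figures are exact complements, and no reason is given for a 33% floor.

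Retention is one of three criteria for confirming feasibility, and the Discussion says that the results will be used to plan fully powered trials. A mark this low would do little to warn the sponsor of heavy attrition. The month-6 results could then describe a small, self-selected group of remaining users.

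**Working it through.** **Inputs.** p = 0.67, 95% confidence (z = 1.96), margin d = 0.075 and n = 151, all from Sample size. Retention mark 0.33, from Secondary outcomes. Tolerated fall in logins 0.33, from Primary outcome.

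**1. The plan's own figure.** For the precision of a single proportion, n = z²·p(1−p)/d² = 1.96² × 0.67 × 0.33 / 0.075² = 151.0. The stated 151 reproduces. The formula therefore uses 67% as a proportion of 151 participants. Because p(1−p) is symmetric, p = 0.33 also gives 151, so the sample size cannot show which figure was meant for retention.

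**2. What the mark accepts.** 0.33 × 151 = 49.8, so 50 retained is enough. Then 151 − 50 = 101 are lost, and 101/151 = 66.9%.

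**3. Adherence counted among all 151.** With 50 still active, adherence at the end can be at most about 50/151 = 33%. The premise needs 0.67 × 151 = 101.2, that is 102 people. The planned interval, 67 ± 7.5, runs from 59.5% to 74.5%, and 33% lies far below it.

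**4. Adherence counted among those retained.** The half-width is 1.96 × √(0.67 × 0.33 / 50) = 0.130, or ±13.0 points instead of ±7.5. Keeping 151 evaluable at 33% retention would need 151/0.33 = 458 enrolled.

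**5. How weakly the mark discriminates.** Under a binomial model with 151 participants, a true retention of 40% reaches at least 50 retained with probability 0.97. A true retention of 50% does so with probability above 0.999.

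**6. If 33% were the drop-out limit.** At most 49 may be lost, so at least 102 must be retained. The half-width among 102 is 1.96 × √(0.67 × 0.33 / 102) = 0.091, or ±9.1 points. For ±7.5 points among those retained, 151/0.67 = 226 would have to be enrolled.

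**The case against.** Adherence and retention are separate outcomes, and the Sample size section speaks of an adherence rate without saying of whom. The 67% might be no more than the login ratio, 100 minus 33. If adherence is meant among remaining users, 67% adherence and 33% retention can both be true. This stands in part: the denominator is not given. But the formula that yields 151 treats 67% as a proportion of 151 people, and among remaining users the ±7.5 points cannot be kept at the retention mark.

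A reader might infer three stronger things that the documents do not support.

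- **That 33% is an inverted figure.** The signs are suggestive: the complementarity with 67%, the definition through drop-outs, and the 33% tolerated fall. That last use occurs in one place only. The same sentence tolerates 50% of goals and questionnaires missing, so lenient marks are not foreign to this plan. A strict two-week drop-out rule could also be a reason for a low mark.
- **That last-month adherence can never exceed 33% at the mark.** Someone who falls silent late in month 6 may have logged in earlier that month. The article also does not say that a person who returns stays classed as a drop-out. The ceiling is approximate.
- **That feasibility would be confirmed after a two-thirds loss.** All three criteria must pass. If logins were totalled over all enrolled, the remaining third would need to log in about 0.67/0.33 = 2.03 times as often as the average enrolled participant did in the first month. The adherence criterion would then resist heavy drop-out. If it were computed on remaining users, it would not.

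The odd definition of retention could be dismissed as loose wording, since the next sentence plainly gives a proportion retained. That is fair, but it leaves the mismatch with the sizing premise.

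**Conclusion.** The point holds as an inconsistency between a stated success mark and a stated planning premise. No calculation in the plan is wrong. At the mark, 50 of 151 are kept. That leaves either end-of-study adherence of roughly 33% at most among all enrolled, against an assumed minimum of 67%, or a margin of ±13.0 points among those retained, against ±7.5. Neither denominator reconciles the two sections.

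This rests on reading 67% as a proportion of participants, as the formula does, and on drop-outs mostly staying inactive. Whether 33% is a slip or a choice cannot be settled from the documents. Because this is a secondary criterion in a one-arm feasibility study, and the other two criteria must also pass, it should be fixed but does not undermine the whole plan.

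**What to change.** Make three statements in the protocol.

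1. Define retention as (enrolled minus drop-outs)/enrolled at month 6.
2. Say whether 33% is the maximum drop-out or the minimum retention.
3. State that adherence is computed among all enrolled.

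Then reconcile the figures. If 33% is the drop-out limit, restate the mark as retention ≥67%, at least 102 of 151. This only just accommodates the premise: at exactly that mark, nearly every retained participant would have to be adherent to reach 67% of those enrolled. If 33% retained is truly meant, give the reason, correct the 67% premise under Sample size, and state that estimates among those retained would rest on about 50 people (±13 points).

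The cost is a definition, a denominator and one corrected figure. The sample size stays at 151 for estimates among all enrolled. Estimates among those retained will be less precise than ±7.5 points under either choice. The downside is a stricter success mark or a less favourable planning figure on record.

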**Discussion:**

This mobile app was designed to provide a digital solution for the promotion of physical activity in people with osteoarthritis. If the feasibility of delivering a physical activity intervention through the mobile app is confirmed, the efficiency of the tool in improving the quality of life of people with hip and knee osteoarthritis should then be properly investigated.

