### Objectives

The PIANISSIMO feasibility study primarily aims to test the adherence of participants with hip and knee OA to a 6-month intervention for the promotion of physical activity using a dedicated mobile app.

The secondary aims are to assess the retention and acceptability of participants with hip and knee OA to the intervention.

Moreover, the study aims to investigate the daily steps pattern in participants with hip and knee OA during the 6-month intervention and to explore the relationship between physical activity and pain. Finally, physical activity patterns of people with hip and knee OA over the 6-month period following the end of the intervention will be analysed.

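### The acceptability criterion is a share of month-6 answers, although the aim is acceptability among participants; positive answers from 23% of those enrolled could count as good

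*Protocol article*

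**What the plan says.** The aim is set for participants. Objectives states: "The secondary aims are to assess the retention and acceptability of participants with hip and knee OA to the intervention". The Methods part of the abstract agrees: "the acceptability of the app and intervention by the study participants will be evaluated through a questionnaire".

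The instrument is used once. Under Follow-up data: "At the end of the intervention, participants will be invited to give their feedback about the mobile app". Table 2 marks acceptability at the 6th month only. The same section defines a drop-out as someone with two weeks of no interaction with the app, and Study design says that the whole study runs through the app.

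The criterion, under Secondary outcomes, is that at least "70% of responses regarding usefulness, user-friendliness and adaptability to condition are positive". Retention in the same section succeeds with at least "33% of participants at the end of the 6 months will be considered a successful outcome". The three criteria are then joined: "Feasibility will be validated if adherence, retention and acceptability meet the positive outcomes specified above". Nothing ties the acceptability criterion to the number enrolled or to a minimum number of answers.

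**The concern.** The criterion and the aim have different denominators. Someone who stops using the app and does not answer at month 6 leaves the acceptability calculation altogether. If people who find the app unsuitable stop earlier than people it suits, the share among answers lies above the share among participants.

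The other criteria do not supply what is missing. Retention counts those who left but does not show whether they found the app unsuitable. The 50% completion rule under Primary outcome covers all questionnaires over six months and sets no floor for this one.

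The sentence also admits two readings: 70% on each of the three topics, or one 70% pooled over them. A pooled share could pass while fit to the condition, which the Discussion gives as the reason for a dedicated app, scores poorly.

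At stake is what the trial may say about acceptability. It is one of three conditions for a yes/no verdict, and the abstract links that verdict to the next step, an investigation of effect on quality of life: "If the feasibility of delivering a physical activity intervention through the mobile app is confirmed".

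**Working it through.** **Inputs from the protocol article.** N = 151 and 67% (Sample size); retention threshold 33% and acceptability threshold 70% (Secondary outcomes).

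**The plan's own figure.** n = z² p(1 − p)/d² with z = 1.959964, p = 0.67 and d = 0.075 gives 3.841459 × 0.2211 / 0.005625 = 150.99, rounded up to 151. The stated sample size reproduces.

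**Smallest number of positives that passes.** Each person who remains is assumed to answer, giving one positive or negative answer per topic. Remaining r = N × retention, rounded up. Positives needed k = 0.70 × r, rounded up. Share of enrolled = k/151. If none, or all, of those without an answer were positive, the share among enrolled would be k/151 or (k + 151 − r)/151.

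| Retention | Remain and answer (r) | Positives needed (k) | k/151 | Highest possible share among enrolled |
|---|---|---|---|---|
| 33% | 49.83 → 50 | 35 | 23.2% | (35 + 101)/151 = 90.1% |
| 50% | 75.5 → 76 | 53.2 → 54 | 35.8% | (54 + 75)/151 = 85.4% |
| 67% | 101.17 → 102 | 71.4 → 72 | 47.7% | (72 + 49)/151 = 80.1% |

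The first row is the minimum under the retention rule. The 67% row is a scenario: if the login rule under Primary outcome is counted over all enrolled and each remaining user logs in as often as before, about 67% must remain. The article does not say this, so both rows are shown. If some who remain do not answer, the counts fall further. With 80% of 50 answering, 0.70 × 40 = 28 positives pass, and 28/151 = 18.5%.

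**What 70% of enrolled would take.** 0.70 × 151 = 105.7, so 106 positive answers. In the 33% row, 106 − 35 = 71 of the 101 without an answer (70.3%) would have to be positive for the enrolled share to reach 70%. If 30% or 50% of them were positive (assumption), the enrolled share would be (35 + 30.3)/151 = 43.2% or (35 + 50.5)/151 = 56.6%.

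**How strong the selection must be (illustrative; all rates assumed).** Let p be the share of enrolled whom the app suits, and s₁ and s₀ the staying rates of suited and unsuited users. The share among responders is p s₁ / (p s₁ + (1 − p) s₀). With p = 0.60:
- s₁ = s₀ = 0.68: 60%, no bias.
- 0.72 against 0.62: 0.432/(0.432 + 0.248) = 63.5%.
- 0.80 against 0.50: 0.480/(0.480 + 0.200) = 70.6%.

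A true 60% is thus lifted to the threshold when suited users are about (0.7/0.3)/(0.6/0.4) = 1.56 times as likely to stay. A ten-point gap in staying is not enough.

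**Pooled reading.** With three topics answered equally often and two of them at u positive, the third needs only 3 × 0.70 − 2u = 2.1 − 2u. That is 50%, 30% or 10% at u = 80%, 90% or 100%.

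**The case against.** A responder denominator is a normal choice for an opinion questionnaire at the end of use. It keeps whether people stayed apart from whether users liked the app, and retention is judged on participants in its own right. This stands in part. A reader might infer that the whole feasibility verdict describes only those who stayed and answered. The document does not support that, because all three criteria must be met and leaving is counted under retention. What remains is that the acceptability criterion alone does not measure what its aim names.

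A reader might also infer that drop-outs are excluded from the questionnaire, or that the result is certainly inflated. Neither is stated. The invitation goes to participants without exclusion, although few who have stopped using the app are likely to answer through it. The direction of bias is plausible, but no figure in the document shows it. The illustration shows that a materially wrong pass needs strong selection and a true share not far below 70%. No probability of a false pass should be quoted.

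Counting non-answers as not positive turns the figure partly into a second retention test: with 105 or fewer answers it cannot reach 70% even if all are positive. That is right, and it is why the figure should be a labelled lower bound without pass/fail force.

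Counts and percentages are already planned under Statistical analysis, so a reader could compute the enrolled share. True, but the pass rule and the wording of the conclusion would be unchanged.

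Finally, the questions listed under Follow-up data ("if they liked the app and why, if they found that the app was adapted to their health condition" among them) do not name user-friendliness. A reader might infer that it is not asked. Secondary outcomes says that the topic is covered and the questionnaire itself is not shown, so matching questions to topics is detail that an article may leave out. It is no part of this point.

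**Conclusion.** The point holds for the acceptability criterion only. As written, 35 positives among 50 answers (23% of 151) satisfy both the acceptability and the retention thresholds. With 67% remaining, 72 among 102 (48%) do. These counts follow from the article's own figures, assuming 151 enrolled and an answer from everyone who remains. How far the responder share departs from the share among participants is unknown: with 50 answers the latter could lie anywhere between 23% and 90%. Upward bias requires that people whom the app does not suit leave earlier, which is plausible and not shown. The choice between per-topic and pooled scoring is a smaller ambiguity that can change the verdict on the same data. Overall this is a cheap improvement of minor to moderate severity.

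**What to change.** In Secondary outcomes:

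1. Apply the 70% threshold to each of usefulness, user-friendliness and adaptability separately, not to a pooled share.
2. Report the number who answered. Beside the percentage positive among responders, give the percentage positive over all enrolled, with no answer counted as not positive. Label it a lower bound and do not use it as a second pass/fail test.
3. Word the conclusion as *acceptable to those who answered at month 6*, unless the all-enrolled figure also reaches 70%.

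Optionally, compare those with and without a month-6 answer on pain and SF-WOMAC at inclusion. This describes who is missing but does not reveal what they thought of the app.

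The cost is a few lines of text and one small table, with no new data. There are two downsides. The narrower wording will often apply, since 106 positive answers out of 151 are needed to avoid it. The per-topic threshold is also slightly harder to meet than a pooled one.

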### Exploratory outcomes

The physical activity pattern assessed by the evolution of daily steps throughout the 6-month intervention will be analysed. The bidirectional relationship between physical activity (e.g. cumulated weekly steps or peak in daily steps) and pain will be explored. Maintenance of the behaviour changes will be investigated during the 6 months following the intervention. All outcomes and their measurement period are presented in Table 2 and Fig. 1.

**Table 2 Tab2:** Outcomes, their measurement and evaluation period

Outcomes	Measurement	Evaluation period				
		**Baseline**	**Weekly**	**Monthly**	**End of PA intervention (6th month)**	**Between the 6th and 12th months**
Adherence	Connection log	Continuously				
	Rate of goal set		x			
	Rate of questionnaire answered		x			x
Retention	No. of drop outs		x			x
Acceptability	Questionnaire				x	

*PA* physical activity

### Data management

Throughout the study, the sponsor of the project, the Luxembourg Institute of Health (contact: project manager), will be responsible for the monitoring of participants.

### Collecting and data management

It will be granted the protection of privacy and confidentiality to all participants by allocating a unique study identifier with participants’ inclusion number for data collection. The investigator will be responsible for maintaining the anonymity of each participant in the study. Information will be collected for each participant at a defined timeline (Table 2 and Fig. 1) and reported in a standardised clinical data structure (OpenEHR) automatically filled out with data collected by the app. The source documents include the original data extracted from the app that will be stored in the standardised clinical data structure by LIH investigators. The investigator will be the sole person allowed to authorise access to the study source data during monitoring, audits or inspection visits. Data from the PIANISSIMO app will be extracted and stored on a LIH password-protected computer that can be accessed only by registered investigators ([name], [name], [name]). All raw data will be checked monthly by the investigator to ensure that all protocols and ethical guidelines for data collection and analysis are followed. The data manager will use computerised consistency tests in order to flag the presence of non-standard, missing, aberrant or inconsistent data throughout the data transfer process. Study data will be entered through the standardised clinical data structure hosted on OpenEHR software, which allows for real-time data quality control. An interim analysis will be done on the data stored on OpenEHR after half of the participants finish the study (*n* = 75) and again after every additional 20 participants. In order to meet the regulatory requirements, the OpenEHR software complies with the recommendations concerning computerised systems for the management of clinical trials and electronic signatures and standards. Connection to such a server is made through the use of a unique password and identifier specific to each user, which will only give access to participant data. The maintenance and security of the database will be the responsibility of the study’s sponsor. An audit function will be integrated into the software, allowing traceability of the date of data collection as well as any further modifications completed. The encrypted data will then be transmitted to the department responsible for data management via a secure Internet connexion.

